#### Control group: Regular health care treatments (private/public health services)

People belonging to the control group will receive the usual services of their health centres, mainly access to outpatient consultations and, in some cases, private treatments. The duration of these treatments will be estimated by the centres themselves, depending on the patient’s clinical condition and/or demand. A registration of the types of treatment and their duration will be carried out.

With the aim of improving control over the treatments received, those patients will be excluded from the study if they are receiving any MOHO intervention in the private or public service.

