## Materials and methods

### Inclusion and exclusion criteria

The study population (experimental and control group) will be composed of (i) adults aged between 18–50 with (ii) a diagnosis of medium or severe ABI and (iii) a diagnosis of mental disorder following ABI (as recognised in the 5th edition of the Diagnostic and Statistical Manual of Mental Disorders (DSM-5) [42]) presenting behavioural, mood and/or emotional disorder. In addition, (iv) the patient must show difficulties in occupational participation compared with the pre-ABI situation and present occupational needs, as determined by an occupational therapist’s comprehensive assessment plus the patient’s identification of at least two occupational performance problems using the COPM (Canadian Occupational Performance Measure, a more detailed description of the tool in Data collection section of this paper). Patients also must be (v) in a situation of hospital discharge from ABI specialisation units and (vi) domiciled in the same province to which the providing hospital belongs.

Subjects will be excluded if (i) they are in a situation of symptomatological destabilisation with severe functional impairment that, as a priority, requires continued support from specialised mental health units and/or psychiatric or hospital admission, and/or (ii) they were diagnosed prior to the brain injury with a severe mental disorder (e.g., schizophrenia or a major depressive disorder) or dementia, and/or (iii) the cognitive deficits associated with ABI do not allow the agreed establishment of goals autonomously or with minimal support from the main caregiver.

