### Statistical analysis

Data will be analysed on an intention-to-treat basis [61] i.e. results will be analysed using the basis of all participants. For missing data, the multiple imputation method will be used.

All variables will first be checked for normality. To test the effectiveness of the intervention, continuous variables having normal distribution will be analysed by repeated measures analysis of variance, ANOVA (within-subject factors: baseline, intermediate evaluation, final evaluation), comparing the two groups (between-group factors).

Due to the proposed design and the technical feasibility of the experimental group provider site, non-simultaneous recruitment makes the potential exposure to certain external factors unequal for some subjects. These factors may include the season of the year or the phase corresponding to the COVID-19 pandemic situation. To control them, we will explore the differences in the proportion of participants for these variables between the two groups using chi-square tests. If there are differences between groups an ANCOVA will be carry out with these external factors as covariates.

Non-normally distributed variables will be analysed using the Mann-Whitney test for group comparison. Friedman analyses and the Wilcoxon signed-rank test will be used for intrasubject factors. A p value < .05 will be defined as statistically significant. Bonferroni correction will be carried out for planned comparisons.

To determine the contribution of satisfaction with activities on quality of life in people with brain injury and a diagnosis of mental illness, beyond the intervention performed, a hierarchical regression analysis will be performed with the entire sample, including the following variables in model 1: belonging to the intervention group, age and level of functionality. In model 2, in addition to the variables in model 1, the variable satisfaction with the occupation (collected by SDO-OB) will be added.

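### The control-arm exclusion for outside MOHO therapy has no stated timing and covers one arm only: after baseline it conflicts with intention to treat, at entry it is a one-sided criterion

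*Protocol article*

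**What the plan says.** Three places in the protocol article bear on this point.

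- **Control group section.** The comparator is introduced with "People belonging to the control group will receive the usual services of their health centres", which may include private treatments. Next comes the treatment register: "A registration of the types of treatment and their duration will be carried out". The exclusion follows: "those patients will be excluded from the study if they are receiving any MOHO intervention in the private or public service". Its declared purpose is tighter control of what these patients are treated with. No time point is given, and the experimental-group section has no counterpart.
- **Inclusion and exclusion criteria.** This list is written for the experimental and control groups together. It has three exclusions, opening with "Subjects will be excluded if (i) they are in a situation of symptomatological destabilisation with severe functional impairment". None concerns MOHO-based therapy.
- **Statistical analysis.** The analysis set is described thus: "results will be analysed using the basis of all participants", under an intention-to-treat label. Missing data are to be handled by multiple imputation.

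**The concern.** The rule can be read as acting on people who are already controls. It speaks of exclusion from the study, follows directly on the record of what controls receive, and sets no end date. On that reading, a control who begins MOHO-based therapy some months after baseline has to leave the study under one section and be analysed under another.

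The statistical problem is selection on a post-baseline event in one arm only. If controls who find such therapy do better than the rest, removing them lowers the control mean and flatters the intervention. The direction is probable but not certain, because people who seek extra therapy may be doing worse.

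If the rule acts only at entry, the difficulty is smaller but does not vanish. Groups in this trial are not formed by randomisation, so an entry filter applied to one arm can itself create a difference between them.

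**Working it through.** **1. The sections compared under each timing**

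| Question | Rule acts at entry only | Rule acts during follow-up |
|---|---|---|
| Consistent with analysis of all participants? | Yes: the person never becomes a participant | No, unless the person's data are kept, which is not stated |
| Consistent with the common eligibility list? | No: criterion missing from a list meant for both arms | Not an eligibility matter |
| Same in both arms? | No | No |
| Risk | One-sided entry filter in a non-randomised comparison | Selection of controls on a post-baseline event |

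Neither column is free of a problem. The text does not say which applies.

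**2. The plan's own figure**

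Inputs from the sample size section and the study flow chart: d = 0.49, two-sided alpha 0.05, power 0.80, 134 participants, 67 per arm.

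For a two-sample t test, the noncentrality is d × √(n₁n₂/(n₁+n₂)) with n₁+n₂−2 degrees of freedom. With 67 per arm it is 0.49 × √(67×67/134) = 2.836, and power is 0.804. With 66 per arm power is 0.798. So 134 is reproduced exactly, and it is the minimum, with no allowance for losses. (The normal approximation gives 66 per arm, 132 in total.)

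**3. What each choice costs in power**

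The documents give no rate of outside MOHO exposure. Rates of 5%, 10% and 20% of controls are assumed here, and a rate near zero is also possible.

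- *Exclude exposed controls:* d stays at 0.49, the experimental arm stays at 67, and the control arm shrinks.
- *Keep exposed controls, worst case:* each is assumed to gain the full treatment effect, so d becomes 0.49 × (1 − exposure) with 67 per arm and the SD unchanged.

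| Assumed exposure | Controls left if excluded | Power if excluded | Diluted d if kept | Power if kept |
|---|---|---|---|---|
| 0% | 67 | 0.804 | 0.490 | 0.804 |
| 5% | 64 | 0.795 | 0.4655 | 0.763 |
| 10% | 60 | 0.781 | 0.441 | 0.717 |
| 20% | 54 | 0.757 | 0.392 | 0.615 |

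The two power columns refer to different contrasts. Exclusion compares the intervention with controls who had no such therapy. Retention compares it with usual services as they turn out.

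**4. The form of the bias**

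Removing a share f of controls who would have scored δ SD higher than those retained shifts the control mean down by f × δ. If δ is assumed to be 0.5 SD, the shift is 0.10 × 0.5 = 0.05 SD at 10% and 0.20 × 0.5 = 0.10 SD at 20%. At zero exposure it is zero, and if δ is negative the sign reverses. The documents supply neither f nor δ, so this shows how the bias arises and does not estimate it.

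**The case against.** A reader might infer that the plan flatly contradicts itself, so that the exclusion and the intention-to-treat analysis cannot both be followed. The documents do not support that much. The rule is in the present tense and says nothing of therapy started after baseline. The eligibility section uses the same kind of construction for ordinary entry exclusions. Read that way, the rule screens people invited from the waiting list and does not touch the analysis set. This part of the objection stands: the conflict depends on timing that the article leaves open.

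Even on the follow-up reading, the article does not say that data already collected are discarded, and multiple imputation could cover what is missing. That is fair, but it does not settle the matter, because the article does not say that an excluded control remains in the analysis.

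The control-only wording also has an evident reason, since the experimental arm receives a MOHO-based intervention by design. That explains why the rule cannot be copied unchanged. It does not prevent a common criterion about therapy received outside the trial.

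Exposure may be low. The introduction describes scarce specialised resources, and the limitations section says this is the first such initiative in the region. Against that, controls may use private treatments, and the introduction calls MOHO the most widely used occupation-focused model. The rate is unknown.

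Finally, keeping exposed controls can cost more power than excluding them, as the table above shows. This stands and must be weighed. It is the price of comparing with the usual services received, and it does not justify one-sided removal under an intention-to-treat label.

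A condensed article may leave detail to a fuller document. Here, however, the article states the rule itself, for one arm and apart from the common list, so the point concerns what is written.

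**Conclusion.** The concern holds in conditional form. The exclusion has no time limit, applies to one arm, and lies outside the eligibility list meant for both groups. Applied after baseline, as its placement suggests, it conflicts with analysing all participants and selects controls on a post-baseline event, probably in favour of the intervention. Applied only at entry, it causes no intention-to-treat conflict, but it is a control-only criterion in a non-randomised trial. Either way, the three sections need reconciling.

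The size of any bias cannot be estimated from the documents. A reader might also infer that the comparator ceases to be usual care. That goes too far: the same section that names usual services adds the exclusion, so the arm can be read as usual services without MOHO-based therapy. All the power figures for exclusion and retention rest on assumed exposure, and the retention figures also assume the full effect in exposed controls. If exposure is near zero, the choice has no practical effect on the result.

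**What to change.** Reconcile the eligibility, control-group and statistical analysis sections as follows.

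1. Add to the common exclusion criteria, assessed at baseline in both arms: currently receiving a MOHO-based intervention outside the trial.
2. In the control-group section, replace the open-ended exclusion with a statement that a control who starts such an intervention after baseline stays in follow-up and in the intention-to-treat analysis.
3. In the statistical section, name a sensitivity analysis that uses the existing treatment register. For example, outcomes measured after the start of outside MOHO-based therapy could be set to missing and multiply imputed, with the result reported beside the main analysis.

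The cost in text is a few sentences. The controls' register is already planned, and the only new item is the baseline question in the experimental arm. The statistical cost is dilution if exposure is common. Since 134 includes no margin, the sponsor should judge the likely exposure from local knowledge before settling the wording.

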### Data collection

Outcome variables will be assessed in both study groups at the beginning of the COT-MHABI protocol, 6 months after the start of the protocol, and after the end of the protocol (12 months) using the scales detailed in Table 2. The collection will be carried out by different researchers. To minimise potential discrepancies, one researcher will allways evaluate the same participant.

**Table 2 pone.0274193.t002:** Tests and variables used in the data analysis.

Test	Outcome variable definition	Scores and Domains	Reliability
*Main outcomes*			
WHOQoL-BREF	Quality of life	**Quality of life (Total score: Min 26-Max 130)** (Domains: general QoL, health status satisfaction, physical health, psychological health, social relationship and environment)	ICC = 0.87
COPM	Self-perceived occupational performance	**Performance change**: difference between measures in self-perceived occupational performance **(Total score: Min 0-Max 50)** **Satisfaction change**: difference between measures in occupational performance satisfaction **(Total score: Min 0-Max 50)**	r = 0.87–0.88
*Secondary Outcomes*			
SOD-EO	Satisfaction with daily occupation, occupational balance and activity level	**Satisfaction (Score: Min 13-Max 91)** Activity level (Score: Min 0-Max 13) Occupational Balance (Score: profile, no min or max) (Domains: productivity, leisure, home tasks and selfcare).	r = 0.84–0.92
RCv3	Satisfaction with performed roles	**Satisfaction (Score: Min 0.00-Max 1.00)** Number of performed roles (Score: Min 0-Max 10) Participation (Score: Min 0.00-Max 1.00) Desired Performance (Score: Min 0.00-Max 1.00)	r = 0.74–1.00
ACS	Perceived activity participation level	**Percentage of maintained activities after ABI (Total score: Min 0%-Max 100%)** (Domains: instrumental activities, low physical demand leisure activities, high physical demand leisure activities, social and educational activities)	r = 0.88–0.95
CIQ	Community integration and participation	**Community integration and participation (Total score: Min 0-Max 29)** (Domains: home integration, social integration and productivity)	r = 0.83–0.93
FIM	Functional Independence	**Functional Independence (Total score: Min 18-Max 126)** (Domains: motor and cognitive)	ICC = 0.85

#### Main outcomes

*Quality of life*. This will be measured by the WHOQoL-BREF (World Health Organization Quality of Life-BREF, Spanish version) [45,46]. This is a generic self-administered questionnaire created by the Quality of Life Study Group of the World Health Organization (WHO). The instrument has 26 questions, two general questions on quality of life and satisfaction with health status, and 24 questions grouped into four areas: Physical Health, Psychological Health, Social Relationships and Environment. Higher scores indicate better perceived quality of life. A 5-point Likert-type response scale is used. The WHOQoL-BREF shows excellent reliability (ICC = 0.87) for the quality of life variable in ABI due to traumatic brain injury [47].

*Perceived occupational performance and satisfaction with performance*. This will be evaluated by COPM (Canadian Occupational Performance Measure, Spanish version) [23,48], which is a self-administered occupational therapy measure based on client-centred practice that helps to establish occupational needs. It assesses changes in self-perceived occupational performance and satisfaction with occupational performance following intervention. The COPM shows excellent reliability (r = 0.87–0.88) in stroke patients [49].

#### Secondary outcomes

*Satisfaction with occupations and occupational balance*. This will be measured using the SDO-OB scale (Satisfaction with Daily Occupation and Occupational Balance, SDO-OB, Spanish version (SOD-EO)) [50,51]. The instrument assesses satisfaction in thirteen occupational areas, organised in four domains (productivity, leisure, housework and self-care) in terms of the person’s activity level, occupational satisfaction and balance. Satisfaction level scores are answered based on a 7-item scale. The scale shows excellent reliability in mental health [52], both for performance satisfaction (r = 0.84) and activity level (r = 0.92). The version translated and validated in the Spanish context has shown good psychometric properties for the population with mental health disorders.

*Participation and satisfaction with the performed roles*. This will be evaluated by RCv3 (Role Checklist Version 3: Participation and Satisfaction, English version) [53]. The instrument assesses the person’s perception of role performance, role satisfaction, and desire to participate in other roles in the future. This version has shown acceptable to excellent test-retest reliability for current role perception (κ = 0.74–1.00), desired future performance (κ = 0.77–0.98), and satisfaction with performance (α = 0.77–0.98) in the general population [54,55].

*Self-perceived level of participation in activities*. This will be measured using the ACS scale (Activity Card Sort, Spanish version) [56]. This is an instrument composed of a total of 89 photographs, used in occupational therapy to perform a joint exploration with the person, noting a catalogue of activities performed in all areas, both before and after the injury or situation that interferes with performance. It is useful to identify loss of participation, set goals and analyse evolution. The items include 20 instrumental activities, 17 social activities and 35 leisure activities of low physical demand and 17 of high demand. The original scale presents adequate psychometric characteristics, with an excellent level of test/retest reliability (r = 0.88–0.95) [56].

*Community integration*. This will be measured from the results collected in the CIQ (Community Integration Questionnaire, Spanish version) [57]. It assesses the limitations in the performance of social roles and community interaction of people with ABI. It presents three main dimensions: domestic integration, social integration and productivity. The total score range is between 0–29 and most items have a range of 0–2. Higher values represent greater community integration and independence. The test-retest reliability of this scale is excellent for this population (r = 0.83–0.93) [57,58].

*Functional independence*. This will be valued from the FIM scale (Functional Independence Measure, Spanish version) [59,60]. The scale represents a uniform measurement system for disability based on the International Classification of Impairment, Disabilities and Handicaps. It assesses six functional areas (self-care, sphincter control, transfers, locomotion, communication and social cognition) within two domains (motor and cognitive). Each item is scored on a 7-point Likert-type scale. The items are performance-based rather than ability-based and are recorded in a hetero-administered manner. Reliability is excellent for the ABI population [60].

*Satisfaction with the intervention process*. This is a provider hospital’s internal questionnaire (Spanish version). This will be collected qualitatively and quantitatively by regular programme satisfaction questionnaires. In this case, there is one questionnaire for the person participating in the process and another one for the main referring family member, if any. Both questionnaires are composed of seven questions about the subjective perception of the results obtained after the intervention with a 7-point Likert-type response scale. In addition, there are 4 more questions that, with a scale of 1 to 10, aim to collect the opinion of the quality of the intervention. Finally, a section will be included where, in a qualitative manner, the person can express other comments not included in the previous questions.

#### Data management

The data will be coded and stored by the research department of the patient provider, the Institut Guttmann Neurorehabilitation Hospital.

#### Power analysis and sample size calculations

Theoretically, with a two-tailed test, a sample of 134 participants will be needed in order to detect a significant difference in WHOQoL-BREF showing an effect size d = 0.49 (alpha = 0.05, beta = 0.20, power = 0.80), according to data collected in Chiu et al. (2016) [47]. The sample was calculated using the GPower 3.1 program.

### Statistical analysis

Data will be analysed on an intention-to-treat basis [61] i.e. results will be analysed using the basis of all participants. For missing data, the multiple imputation method will be used.

All variables will first be checked for normality. To test the effectiveness of the intervention, continuous variables having normal distribution will be analysed by repeated measures analysis of variance, ANOVA (within-subject factors: baseline, intermediate evaluation, final evaluation), comparing the two groups (between-group factors).

Due to the proposed design and the technical feasibility of the experimental group provider site, non-simultaneous recruitment makes the potential exposure to certain external factors unequal for some subjects. These factors may include the season of the year or the phase corresponding to the COVID-19 pandemic situation. To control them, we will explore the differences in the proportion of participants for these variables between the two groups using chi-square tests. If there are differences between groups an ANCOVA will be carry out with these external factors as covariates.

Non-normally distributed variables will be analysed using the Mann-Whitney test for group comparison. Friedman analyses and the Wilcoxon signed-rank test will be used for intrasubject factors. A p value < .05 will be defined as statistically significant. Bonferroni correction will be carried out for planned comparisons.

To determine the contribution of satisfaction with activities on quality of life in people with brain injury and a diagnosis of mental illness, beyond the intervention performed, a hierarchical regression analysis will be performed with the entire sample, including the following variables in model 1: belonging to the intervention group, age and level of functionality. In model 2, in addition to the variables in model 1, the variable satisfaction with the occupation (collected by SDO-OB) will be added.

The quantitative analyses will be carried out using SPSS 25.0 (IBM Corporation, Armonk, NY). A qualitative thematic analysis of the responses obtained in the open-ended questions of the satisfaction questionnaires will be carried out. The analysis to be carried out will be inductive, and no pre-established categories will be used prior to coding. Three researchers will analyse the written fragments and will carry out an axial coding initially, and then carry out a selective coding, generating themes and categories. This analysis will be carried out using the Atlas.ti version 9 program.

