### Recruitment methods

For both the experimental and control groups, the referral of patients to the study will take place through the neuropsychiatry department of the Institut Guttmann Neurorehabilitation Hospital in Badalona (Spain), which does not participate in the al-location of subjects, protocol intervention, data collection, or statistical analysis of the results. This department will assess mental health baseline status using the Neuropsychiatric Inventory Questionnaire (NPI-Q)) [43], evaluating possible interference with the results of concomitant pharmacological treatment.

Regarding the allocation, the experimental group will be composed of patients that will receive the COT-MHABI intervention protocol, framed within a community intervention programme at the hospital, after discharge. As it is a very specific and novel intervention, the resources for its implementation are limited, generating a waiting list (over 12 months). Given that this standby period is longer than the duration of the intervention in the experimental group, patients on the waiting list will be invited to participate in the control group with the consideration of receiving the intervention at a later stage.

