### Trial design and setting

Due to the logistical reasons discussed above, a non-randomised controlled clinical trial will be performed. The measurement points of both groups will be comparable, matching gender, age, geographical area of residence and diagnosis. Fig 1 shows the SPIRIT 2013 schedule of enrollment, interventions, and assessments. Fig 2 includes a flow chart of the main parts of the study methods.

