**Fig 2 pone.0274193.g002:**
[figure not shown]
Study methods flow chart. 134 participants will be assessed for elegibility, allocating 67 in each arm (experimental and control groups). COT-MHABI protocol will be applied in experimental group and regular health care interventions in control group. For both groups, outcomes will be assessed over a one-year period at baseline, by the 6^th^ and 12^th^ month, when data collection is closed and analysis begins.

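### Calendar time is left out of the matching although recruitment is admitted to be non-simultaneous, and the only remedy is a test-triggered ANCOVA that weakens as the arms overlap less in time

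*Protocol article*

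**What the plan says.** Four places in the protocol article bear on this point.

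- **Trial design and setting.** Allocation is not random: "a non-randomised controlled clinical trial will be performed". Comparability is to come from matching: "The measurement points of both groups will be comparable, matching gender, age, geographical area of residence and diagnosis". Date of entry is not listed.
- **Recruitment methods.** Treatment capacity is limited, which creates a waiting list of over 12 months, longer than the intervention itself. From that list, "patients on the waiting list will be invited to participate in the control group".
- **Statistical analysis, on timing.** The design and the feasibility of the site treating the experimental group are given as reasons why "non-simultaneous recruitment makes the potential exposure to certain external factors unequal for some subjects". Season and pandemic phase are the examples.
- **Statistical analysis, on the remedy.** The two groups' distributions over these factors are compared by chi-square tests. If they differ, the factors enter an ANCOVA as covariates. Non-normal outcomes go to a Mann-Whitney comparison, with no adjustment for these factors stated.

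**The concern.** Without randomisation, nothing balances calendar time between the arms except what the plan does about it. The plan identifies calendar time as a source of unequal exposure, matches on four other factors, and leaves this one to the analysis. Pandemic phase could plausibly act on quality of life, activity participation and community integration, all of which are outcomes here.

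The remedy has three limits:

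1. It depends on a significance test, which can miss a modest imbalance.
2. As written, it does not reach outcomes analysed by Mann-Whitney.
3. Adjustment for period works only where both arms were observed in the same period. The smaller the overlap, the more precision it costs, and with no overlap it cannot work at all.

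The waiting list offers a way to limit the problem beforehand. Untreated eligible patients are waiting while others are being treated, so at least some controls could start close in time to their matched treated participant. The article gives no reason why control baselines could not be paced in this way.

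**Working it through.** **Inputs from the article.** The sample size section states "with a two-tailed test, a sample of 134 participants will be needed", "showing an effect size d = 0.49 (alpha = 0.05, beta = 0.20, power = 0.80". The caption of Fig 2 gives "allocating 67 in each arm (experimental and control groups".

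**The plan's own figure.** A two-sample, two-sided t test at d = 0.49, alpha 0.05 and power 0.80 needs 66.35 per arm, hence 67 per arm and 134 in total. This matches the article. Power at 67 per arm is 0.804 by the noncentral t and 0.810 by the normal approximation. The sample size is not in dispute.

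**Assumptions.** The article gives neither the imbalance nor the size of a period effect. Take a two-level period with half of all participants in each level, and let a be the difference between arms in the proportion falling in one level. The calculation treats a single between-group contrast.

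**Precision cost of adjusting.** The correlation between group and period is then a, so the variance of the adjusted group effect is inflated by

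VIF = 1 / (1 − a²).

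Without inflation, SE = √(2/67) = 0.173 SD and d/SE = 0.49/0.173 = 2.836. Power ≈ Φ(2.836/√VIF − 1.96).

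| Split | a | VIF | √VIF | 2.836/√VIF | Power (normal) | Power (noncentral t) |
|---|---|---|---|---|---|---|
| 50/50 | 0 | 1.00 | 1.00 | 2.836 | 0.81 | 0.80 |
| 75/25 | 0.5 | 1.33 | 1.15 | 2.456 | 0.69 | 0.68 |
| 80/20 | 0.6 | 1.56 | 1.25 | 2.269 | 0.62 | 0.61 |
| 90/10 | 0.8 | 2.78 | 1.67 | 1.702 | 0.40 | 0.38 |
| 100/0 | 1 | undefined | – | – | not estimable | not estimable |

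The noncentral t column uses an effective 67/VIF per arm. The two methods agree to within 0.02.

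**The chi-square trigger.** With 67 per arm and a two-level period, the test has power 0.21, 0.64 and 0.94 for imbalances of 10, 20 and 30 percentage points. It often misses a modest imbalance and rarely misses a large one.

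**Does the trigger do damage where it misses?** The chi-square-then-ANCOVA rule was simulated with a normal outcome, a correctly coded two-level period, period effects of 0.3 and 0.5 SD, and 4000 runs per scenario. Type I error stayed at about 4% to 6% for imbalances of 10, 20 and 30 points. The rule is therefore tolerable for normal outcomes at modest imbalance.

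**Where no adjustment is made.** This is the position for a Mann-Whitney outcome as the plan is written. A single-time group contrast carries a bias of a × period effect. At a = 0.2 and period effects of 0.2 to 0.5 SD, that is 0.2 × 0.2 = 0.04 to 0.2 × 0.5 = 0.10 SD. A t test on such data would have type I error of 5.6% to 8.9%, which serves as a guide to the order of size for a rank test.

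**The case against.** The strongest reply is that the problem is disclosed, may be small, and already has a remedy. Most of that stands.

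- **Degree of separation.** A reader might infer that the arms are recruited one after the other and that period is built into the contrast. The article does not say so. It speaks of potential exposure, unequal for some subjects, and a waiting list that exists because others are being treated points to at least some overlap. The large splits in the table are hypothetical.
- **Size of bias.** A reader might compute that a 75/25 split with a 0.3 to 0.5 SD period effect gives a bias of 0.15 to 0.25 SD, or 31% to 51% of d = 0.49. That is the bias of an unadjusted single-time comparison. For normal outcomes the plan would almost surely not leave it in place, since the chi-square test already has power 0.94 at 30 points. The planned model also has repeated measures: a shift that is constant over a participant's follow-up cancels in change from baseline. Baseline and month 12 fall in the same season, so a stable seasonal effect largely drops out of the 12-month change. Month 6 and a changing pandemic phase stay exposed.
- **Feasibility.** A reader might infer that controls can be enrolled at any time. They cannot: a control needs about 12 months of waiting still ahead, so the usable pool is mainly recent entrants to the list. The Limitations section also reports difficulty in finding eligible patients. That controls can be paced to treated starts is an inference from Recruitment methods and holds only for part of the list.
- **Condensed article.** Enrolment windows may be set in a fuller protocol. But the article states its matching factors and its remedy for timing, and the point concerns those as stated.

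These replies limit the size of the point. They do not answer the precision lost as overlap shrinks, the dependence on a significance test, or the silence on Mann-Whitney outcomes.

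**Conclusion.** The point holds as a worthwhile improvement in design. It does not show that the comparison is invalid. The plan concedes possible unequal exposure to calendar factors, does not match on calendar time, and relies on an adjustment that is conditional, is not stated for non-normal outcomes, and loses power as the arms separate.

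The size is conditional on the assumed two-level period, its even overall split, and the imbalance. Power falls from about 0.80 to about 0.69, 0.62 and 0.40 at splits of 75/25, 80/20 and 90/10, and the effect is not estimable with no overlap. At imbalances of 10 to 30 points, normal outcomes are adequately protected by the planned rule. The actual imbalance cannot be read from the article.

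**What to change.** **Trial design and setting.** Add calendar date of baseline to the matching as a target. Where the waiting list allows, invite each control with at least 12 months of expected wait remaining, so that baseline falls in a set window (for example the same calendar quarter) around the matched treated participant's start.

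**Statistical analysis.** Adjust for calendar period whatever the chi-square result, and state how this is done for outcomes that would otherwise go to Mann-Whitney, for instance by a rank test stratified by period.

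**Cost.** No extra patients or visits. If the window is largely met, the imbalance is near zero, so VIF is near 1 and 134 participants keep power of about 0.80. Adjusting in every case is cheap when balance is good: at a 20-point imbalance VIF = 1/(1 − 0.04) = 1.04 and power is 0.79. The real price is harder matching in a scarce population. The tolerance on another factor, such as age, may need to be wider, and accrual could slow if the window were made an absolute condition.
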